### Pilot Study

Prior to the main study, a pilot study was conducted between March and May 2007. One hundred adolescents of both sexes of similar age to those recruited for the main study were selected to check the feasibility, understanding and reliability of the questionnaires. Similarly, the feasibility of the planned timetable for acquiring body composition and physical fitness data in the convenience sample was verified. The pilot study also served to train evaluators and standardize planned protocols of data collection.

### Data Collection

Data collection for Study 1 was undertaken by the epidemiological research group in the selected classrooms. The adolescents were requested to complete a questionnaire, which took 60 to 90 minutes. At the end of this session, the researchers gave another questionnaire to each adolescent for both their mother and father to fill out (Study 2) to be handed in a week later.

For Study 3, data were collected over three consecutive weeks over the period November 2007 to February 2008. To recruit the adolescents, all the classes in one of the schools participating in the epidemiological study (Study 1) were invited to participate. Since we were unable to obtain a sample of 200 boys and girls from one school, a second school was invited to cooperate. Informative meetings were organized for the adolescents and their parents at the schools. At these meetings written information was provided detailing the project's objectives and how they would be contributing to the study. For the physical examination and biological sample collection, the adolescents and at least one of their parents or legal guardians signed an informed consent form. Figure 1 shows the data collection process in the convenience sample.

**Figure 1 F1:**
[figure not shown]
**Diagram showing the logistics of data collection for Study 3**.

### Variables and study instruments

The questionnaire used for Study 1 assesses health status and was based on previous questionnaires used in several national and international health surveys conducted in adolescents [27-30]. This questionnaire was prepared by selecting the questions most suited to our research objectives. Additionally, some questions were designed by the researchers to obtain information on the prevalence of infections and allergies. This aspect has not been considered in any of the previous questionnaires. We also incorporated a specific questionnaire from the AVENA Study about food intake [31], as well as the SCOFF questionnaire [32] in its Spanish version [33] that assesses the risk of eating disorders, and 2 questionnaires designed to measure physical activity and sedentary habits: the Spanish adaptation of the Physical Activity Questionnaire for Adolescents [34], and an adaptation of the Sedentary Habits Questionnaire for Adolescents used in the HELENA Study [35]. To determine physical activity and food consumption habits during break time, two additional questionnaires designed by our research group were included: Recess Physical Activity Questionnaire (RPAQ) and Recess Food Intake Recall (RFIR). The main topics covered by the complete questionnaire are provided in Table 1.

**Table 1 T1:** Categories assessed in the questionnaires

		Adolescents' questionnaire	Parents' questionnaire
Health Status	Chronic disabilities	√	√
	Back pain	√	√
	Infections	√	
	Allergies	√	
	Body mass index	√	√
	Eating disorders	√	√
	Medication	√	
	Dental care	√	
Lifestyle Indicators	Physical activity	√	√
	Physical activity beliefs and attitudes	√	√
	Sedentary habits	√	√
	Physical activity and sedentarism in school recess	√	
	Food intake	√	√
	Food intake in school recess	√	
	Dietary patterns	√	√
	Tobacco	√	√
	Alcohol	√	√
	Academic performance	√	
	Academic beliefs and attitudes	√	

Adolescents' questionnaire administered in Studies 1 and 3. Parents' questionnaire administered in Study 2.

For Study 2, information was gathered via a questionnaire specifically designed for the parents. Questions related to the incidence of infections or allergies in the adolescents were also included to assess the validity, via a multiple-informant process, of the replies provided by the adolescents and parents. In addition, parents were questioned about their own health status and lifestyle. Two questionnaires about physical activity and sedentary habits were incorporated into the parents' survey: the International Physical Activity Questionnaire (IPAQ) [36] and the sedentary habits questionnaire used in research on adolescents adapted for adults. The main health and lifestyle topics included in the final questionnaire administered to the parents are provided in Table 1.

In addition to the assessments undertaken in Studies 1 and 2, the health status of the subjects participating in Study 3 was assessed in detail. The following list provides the additional determinations made in this subset of 200 volunteers:

#### Body composition

Body mass index (BMI) was calculated as weight (kg) without shoes and with light-weight clothing, divided by height (m) squared. Weight was measured using a standardized scale ± 0.05 kg. Height was measured using a statiometer ± 1 mm incorporated into the scale. Skinfold and body circumference measurements were obtained according to the protocol used in the AVENA Study in which anthropometric measurements were made in over 2500 Spanish adolescents [37].

The following skinfold measurements were made on the left side of the body to the nearest 0.1 mm using a skinfold caliper (Caliper Holtain; Holtain Ltd., Wales, UK): (1) triceps, halfway between the acromion process and the olecranon process; (2) biceps, at the same level as the triceps skinfold, directly above the centre of the cubital fossa; (3) subscapular, about 20 mm below the tip of the scapula, at an angle of 45° to the lateral side of the body; (4) suprailiac, about 20 mm above the iliac crest and 20 mm towards the medial line; (5) thigh, at the midline of the anterior aspect of the thigh, midway between the inguinal crease and the proximal border of the patella; (6) calf, at the level of maximum calf circumference, on the medial aspect of the calf. Circumferences were measured using an nonextensible metric measuring tape (Seca 200; Seca, Hamburg, Germany) to the nearest 1 mm on the: (1) biceps; (2) contracted biceps; (3) waist; (4) hip; and (5) calf. Each set of anthropometric measurements was taken twice.

Bioelectrical impedance was determined using AKERN 101 equipment (AKERN Srl., Firenze, Italy). This method has been previously used in adolescents [38,39]. The AKERN 101 body impedance analyser uses a classical tetrapolar technique, whereby a constant sinusoidal current is injected at a fixed frequency of 50 KHz. The current level is kept constant at 800 microamperes on overall loads ranging from 1 to 4000 ohms. Subjects removed their socks, shoes and any metal jewellery before measurements.

Blood pressure was measured at the same time of the day using a validated digital automatic blood pressure monitor (OMRON M6, OMRON HEALTH CARE Co., Ltd., Kyoto, Japan) according to the International Protocol of the European Society of Hypertension [40]. Sexual maturity was assessed following the methodology described by Tanner and Whitehouse [41], which distinguishes 5 stages according to genital development and pubic hair in males, and breast development and pubic hair in females.

#### Physical activity and energy expenditure

To more precisely assess the physical activity and inactivity patterns of the subset of adolescents, besides completing the questionnaire, each subject was requested to keep a diary of energy expenditure and wear an ActiGraph GT1M accelerometer. This small lightweight uni-axial accelerometer has been widely validated for use in children and adolescents [42]. Following consensus recommendations [43], the subjects wore the accelerometer for 7 days. The level of activity was recorded in the instrument's memory every 15 seconds (15-s epoch) as recommended for this age group. Additionally, during the time the subjects wore the accelerometer, they completed the Bouchard 3-day activity diary [44]. The activity diary estimates the total daily energy expenditure of each subject on Thursday, Friday and Saturday. This diary divides each day into 96 15-min periods. The subject is instructed to think about the amount of energy expended during each 15-min period and record it using a scale of 1 to 9 according to the instructions in the diary.

#### Health-related fitness assessment

The tests selected for the evaluation of health related fitness in the AFINOS Study form part of the EUROFIT and FITNESGRAM batteries used to assess the components of physical fitness associated with health [45,46]. This methodology has been used in the AVENA and HELENA studies to assess adolescents aged between 13 and 16 from Spain and other European countries [47]. Below, we describe the specific tests performed.

##### Course-navette or 20-m shuttle run test

This test is probably the most frequently used to assess cardio-respiratory capacity in children and adolescents [48]. The subject runs a distance of 20 metres without interruption according to the pace marked by the test protocol. The pace of the test is ramped such that running speed increases by 0.5 km/h each minute or period. The test is finished when the subject is unable to complete the 20 metre distance within the specified time period marked by a loud signal. The last completed run indicates the final result of the test.

##### Handgrip strength

Using a handheld dynamometer (TKK 5101; Takei, Tokyo, Japan) the maximum isometric force that the musculature of the hand and arm can generate was determined. The subjects were allowed 2 attempts per hand in a standing position with the arm completely extended without touching any part of the body. The optimum grip of the dynamometer in adolescents is adjusted according to the size of the hand and the sex of the subject [49].

##### Flexed arm hang

This test measures the amount of time that the subject can maintain the maximum voluntary contraction while hanging from a bar (palms outward). The arms, shoulders and dorsal musculature force should remain with the body in the "up" position for as long as possible.

##### Trunk lift

The strength and flexibility of the trunk extension is measured by having the subject lie face down on a mat, elevating the upper portion of his body using the back muscles. This position is maintained while the distance between the chin and floor is measured.

##### Sit-up

This test included in the EUROFIT battery, measures the abdominal strength of each subject. The participants lie face up with their hips and knees at a 90° angle. The ankles rest on a chair and the arms are crossed over the chest with each hand placed on the opposite shoulder. From this position the subject contracts the abdominal muscles and sits up to touch his knees with his elbows. The number of repeated abdominal contractions accomplished in one minute is measured.

##### Bosco jumps

To evaluate the strength of the lower half of the body, the protocol proposed by Bosco [50] for use on the Bosco System force platform was used (ERGOJUMP-Plus BOSCO SYSTEM^®^; Byomedic, S.C.P., Barcelona, Spain). Three kinds of vertical jumps are performed: squat jump, countermovement jump, and abalakov. The subject performs the three types of jump on the platform and the Bosco System calculates the height of the jump from the amount of time spent in the air during the jump. In addition to determining the explosive strength of the lower extremities, the results obtained from the three jumps allow assessment of the coordination index and elasticity index.

##### Standing broad jump

Standing with feet together, the subject jumps as far as possible from a horizontal line. The score equals the distance between the starting line for the jump and the subject's heels.

##### 4 × 10-m shuttle run

Adapted from the 5 × 10-m included in the EUROFIT battery, the objective of this test is to assess motion velocity, agility and coordination. The subject runs 10 meters back and forth 4 times, as fast as possible. In each 10 metre run, the subject picks up a sponge, then runs back 10 metres, drops the sponge and picks up another sponge, repeating the same actions two more times, using a total of three sponges during the test (for the first 10 m run the subject does not carry a sponge).

##### Back saver sit and reach

this test included in the FITNESSGRAM battery measures the flexibility of the subjects using a standard size box. With one foot up against the front side of the box and the other leg flexed, the subjects must stretch the longest distance possible from a seated position. The back-saver sit and reach assesses the flexibility of each leg independently, whereas the traditional sit and reach assesses the flexibility of both legs together.

#### Haematological and biochemical profiles

A fasting blood sample was obtained from the cubital vein in the early morning at the schools attended by the adolescents in the subset. 16 ml of blood was drawn from each subject and aliquoted into: 1 tube containing EDTA (4.5 ml), 1 tube containing EDTA (1.5 ml), and 1 tube containing dry gel for serum (10 ml). Given the labile nature of some of the molecules to be analyzed, the tube containing 1.5 ml of anticoagulated blood with EDTA is processed *in situ *with aprotinin as protease inhibitor [51]. Once the blood was extracted, it was immediately transported to the Instituto del Frio where the 4.5 ml of anticoagulated blood in EDTA was aliquoted into 2 parts and one sent to an outside laboratory to obtain haemogram data and the other one immediately analyzed in the CSIC laboratory to determine lymphocyte subpopulations. The remainder of the blood (EDTA treated and dried gel) was centrifuged, plasma and serum removed and then frozen at -80°C to be analyzed later.

The haematological study (haemogram) was performed using an automatic cell counter (ABX 120DX Horiba, Spain). The variables obtained were: (1) red blood cell, white blood cell, neutrophil, lymphocyte, monocyte, basophil, eosinophil and platelet counts and leukocyte profile; and (2) haemoglobin concentration, haematocrit and the haematic indices: mean corpuscular volume (MCV), mean corpuscular haemoglobin (MCH), concentration of mean corpuscular haemoglobin (CMCH), and red cell distribution width (RDW).

The biochemical profile included: 1) the plasma lipid triglycerides, total cholesterol, HDL-c, LDL-c (by enzymatic colorimetric methods) and apolipoproteins B and A1 (by turbidometry); and 2) the metabolic regulators glucose, total proteins, iron, urea and uric acid (by enzymatic colorimetric methods), ferritin and pre-albumin (by turbidometry). All determinations were analysed in serum by using an AU2700 Olympus analyser.

#### Immunological profile

A novel feature of this study was the inclusion of immunological variables based on the results of previous studies such as AVENA and HELENA [31,35]. The following determinations were made with the objective of maximizing the available resources.

##### Cell-mediated immune system

(1) the lymphocyte subsets CD3+ (mature T lymphocytes), CD4+ (T helper lymphocytes), CD8+ (T cytotoxic lymphocytes), CD16+/56+ (natural killer cells), CD45RA+ and CD45RO+ (native and memory T cells, respectively) determined by flow cytometry according to Baker [52]; (2) "in vivo" cell-mediated immune function through the analysis of serum cytokines: IL-2, IL-4, IL-5, IL-10, TNF-α, IFN-γ, IL-8, IL-1β, IL-6) by flow cytometry and TGF-β by Enzyme-Linked ImmunoSorbent Assay, ELISA

##### Humoral immune system

(1) the lymphocyte subset CD19+ (B lymphocytes) by flow cytometry according to Baker [52]; (2) humoral immune function assessed via serum immunoglobulins (Ig G, A, M) by turbidimetry using the AU 2700 (Olympus) and Ig E measured using the chemoluminescence instrument ADVIA CENTAUR (Siemens).

##### Innate immune system

serum complement factors C3 and C4 by turbidimetry (AU 2700) (Olympus); and (2) acute phase proteins: serum C-reactive protein by turbidimetry (AU 2700) (Olympus), and serum caeruloplasmin levels measured by nephelometer (Nephelometer Behring) (Dade-Behring).

##### Hormones and adhesion molecules

(1) the serum cell adhesion molecules sE-selectin, sICAM-1, sVCAM-1 by flow cytometry, sL-selectin by ELISA; (2) adipocytokines in serum via adiponectin by flow cytometry; (3) the gut hormones ghrelin, insulin, leptin, peptide YY in plasma treated with aprotinin analyzed by flow cytometry; and (4) the pituitary hormones thyroid stimulating hormone (TSH), luteinising hormone (LH), follicle-stimulating hormone (FSH), growth hormone (GH), prolactin, adenocorticotropic hormone (ACTH) by flow cytometry.

#### Ethical aspects

The study was conducted according to the ethical standards established in the 1961 Declaration of Helsinki (as revised in Hong Kong in 1989 and in Edinburgh, Scotland, in 2000). The AFINOS Study was approved by the Ethics Committee of the Puerta de Hierro Hospital (Madrid, Spain) and the Bioethics Committee of the Spanish National Research Council. Before participating in this study, all adolescents were informed of the nature of the study and gave their consent; parents also provided written consent. The data collected as well as any documents generated were numerically coded for anonymity and protection from unauthorized use by people not involved in the study. The information gathered in this study is strictly confidential. However, the participants and their parents were informed that the information could be accessed by the Spanish Health Authorities under the Law of Data Protection (LOPD 15/1999) covered by Spanish Law.

#### Statistical analysis

The final data will be analyzed using SPSS and SAS software. Frequencies and distributions of the variables will be determined using descriptive statistics that will serve to determine the general situation of the study subjects. Quantitative variables will be expressed as means and standard deviations of the mean, except for age, which will be expressed as year-by-year frequencies (13-14-15 and 16), and qualitative variables will be expressed as absolute frequencies of every category and percentages related to the total number of valid cases. The normal distribution of quantitative variables will be checked through adequate tests. To determine possible associations, the Chi-squared test will be used for qualitative observations and the student *t-*test to compare independent means of the quantitative data [26]. Pearson's correlation coefficient will be used to analyse two quantitative variables and if these are not verified as normally distributed the Spearman correlation will be used [53]. When analysis of several variables is needed, a multivariate analysis using the forward stepwise multiple regression method will be performed to construct models to explain the variability observed in the population and assess the combined effect of different variables. Risk profiles will be generated by multiple logistic regression, determining adjusted regression coefficients to calculate the odds ratio for each variable.

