1. To assess the relationship between obesity and susceptibility to infection in the adolescents and their parents.

2. To assess the relationship between physical activity and physical inactivity patterns in the adolescents and their parents.

3. To assess the relationship between the basic eating habits of the parents and basic eating habits of the adolescents involved in the study.

(d) Aims of Study 3 conducted on a subset of 200 adolescents

1. To assess the relationship between physical activity habits, physical fitness level and biochemical and immunological markers.

2. To assess the relationship between body composition (underweight/overweight/obesity) and biochemical and immunological profiles.

3. To assess the relationship between basic eating habits and biochemical and immunological profiles.

4. To assess the relationship between biochemical/immunological profiles and allergies, infections and cardiovascular risk factors.

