The study has several limitations. Self reporting is one of the inherent problems affecting the quality of the information obtained in any inquiry through interviews and questionnaires. Infections and allergic processes are subject to seasonal change such that gathering information at one specific point in time will not precisely reflect the prevalence and incidence rates of these disorders. Another possible limitation has to do with the response rates of the parents of the adolescents in the survey process. A reduced response rate could produce an undetermined bias in the responses, which could influence the conclusions drawn from the results.

The limitations of Study 3 are the restricted sample size (n = 200), which is the consequence of the high costs of the immunological study (approximately 600€/subject) and the labour intense data collection process involved in measuring physical activity using the accelerometer. This sample size does not allow for extrapolating results to the population group under study. However, it is sufficiently large to establish relationships among the variables determined. An additional limitation is the non-random selection of the components of the convenience sample, which could introduce a bias associated with the specific characteristics of the school populations of the centres selected.

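### Forward stepwise regression is fixed as the multivariable method, although the Study 3 aims name their exposures in advance; selection can omit the exposure and biases the estimate when it is kept

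*Protocol article*

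**What the plan says.** The Statistical analysis section first lists pairwise methods. It says that "the Chi-squared test will be used for qualitative observations and the student" *t*-test for independent means, and that "Pearson's correlation coefficient will be used to analyse two quantitative variables", with Spearman's coefficient if normality fails. None of these adjusts for a third variable.

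It then turns to multivariable work: "When analysis of several variables is needed", "a multivariate analysis using the forward stepwise multiple regression method will be performed to construct models". For risk profiles it adds a separate method: "Risk profiles will be generated by multiple logistic regression, determining adjusted regression coefficients to calculate the odds ratio for each variable". The section gives no candidate list and no entry criterion.

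The first aim of Study 3 (Study aims, part d) is "To assess the relationship between physical activity habits, physical fitness level and biochemical and immunological markers". Aims 2 and 3 put body composition and eating habits in the place of the exposure. Sexual maturity is recorded in Study 3 (Body composition) by a method "which distinguishes 5 stages according to genital development and pubic hair in males", with a corresponding scale for females.

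On how results will be read, the Discussion concedes that 200 adolescents do not allow extrapolation to the population, then adds: "However, it is sufficiently large to establish relationships among the variables determined". The Conclusions section expects the results to confirm earlier findings on activity and overweight or metabolic disorder.

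**The concern.** Aims 1 to 3 are questions of estimation: how strongly is this exposure associated with this marker, given the obvious confounders? The answer is needed whether it is large, small or null. Forward selection answers another question: which variables pass an entry test in this sample? Three things follow.

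- The exposure may be absent from the final model, so that no estimate is reported for the aim.
- The variables adjusted for can differ by marker, so estimates across a panel of markers are not comparable.
- An estimate is seen only when it is large enough to be selected. It is therefore too large on average, and the usual P value and interval ignore the selection.

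The unadjusted pairwise tests add chance findings over a long marker list, and the Discussion does not present the results as exploratory. At stake is whether the reported activity–immune associations can be taken at face value.

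**Working it through.** **1. Sample size.** 182 × 1.10 = 200.2, which reproduces the stated 200. The effect size behind 182 is not given. I take 182 as the analysable number.

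**2. Markers named in the aims** (biochemical and immunological; counted from the blood-measurement sections):

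| Group | Count |
|---|---|
| Biochemistry: 6 lipids and apolipoproteins + 7 others | 13 |
| Cell-mediated: 6 lymphocyte subsets + 10 cytokines | 16 |
| Humoral | 5 |
| Innate | 4 |
| Hormones and adhesion molecules: 4 + 1 + 4 + 6 | 15 |
| **Total** | **53** |

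The 14 haematology variables would make 67, but aim 1 does not name them.

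**3. Chance findings, one exposure, all nulls true.** Expected number: 53 × 0.05 = 2.65. Probability of at least one, if tests are independent: 1 − 0.95^53 = 93.4%. Correlation between markers would lower the second figure but not the first.

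**4. Noise admitted by forward selection.** With k independent null candidates and entry at 0.05, the chance of at least one entering is about 1 − 0.95^k: 40% for k = 10 and 64% for k = 20. Simulation at n = 200 gives 41% and 66%, and 81% and 96% if entry is at 0.15. Both k and the entry level are assumptions, because the article states neither.

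**5. Selection with a real effect, by hand.** Assume a true slope of 0.15 and a within-sex SD of 1 for activity and for the residual.

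- Standard error ≈ 1/√182 = 0.0741.
- Smallest estimate that reaches 5%: 1.96 × 0.0741 = 0.145.
- Chance of falling below it: Φ((0.145 − 0.15)/0.0741) ≈ 47%. In those samples nothing is reported for the exposure.
- Mean of the estimates above it: 0.15 + 0.0741 × φ(−0.065)/Φ(0.065) = 0.15 + 0.0741 × 0.398/0.526 ≈ 0.206, which is 37% too large.

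**6. The same by simulation of the full procedure.** Ten candidates (activity, sex, eight noise variables), entry at 0.05, a sex difference of 0.6 SD in activity and of 0.3–0.5 SD in the marker:

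- activity is dropped in about 44–49% of runs;
- when kept, its mean estimate is about 0.21–0.22, or 40–45% too large (0.21/0.15 = 1.40);
- activity is in and sex is out in roughly 8% of runs (marker difference 0.5 SD) to about a third (0.3 SD), which adds confounding to the selection bias;
- the model that always contains activity and sex averages 0.15.

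**7. The null case, for balance.** With no true activity effect and sex among the candidates, stepwise keeps activity in about 5–8% of runs, close to nominal.

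**8. Pairwise correlation, for contrast.** If both sexes are analysed together, with assumed sex differences of 0.5–0.8 SD in activity and 0.3–0.8 SD in the marker and no true effect, the correlation is significant in 7–51% of runs at n = 200. With sex retained in a model it is 5.0–5.6%. This concerns the unadjusted tests, not the stepwise models.

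**The case against.** The strongest reply is that this is one paragraph of a condensed article. Covariate lists, entry criteria and multiplicity rules commonly sit in a full protocol or analysis plan, which is not shown. That stands, and silence on them is not the point here. Several stronger readings fall with it:

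- *That sex, age and pubertal stage are left out of the models.* The article names no covariates for any model. Nothing says these are excluded.
- *That pairwise results screen variables into the stepwise model, or that boys and girls are pooled in the pairwise tests.* The section lists methods in an order. It states no screening rule and does not mention pooling.
- *That stepwise models will report confounded associations as findings.* With sex among the candidates and no true effect, the error rate stays near nominal (step 7). The large figures in step 8 belong to unadjusted correlations.
- *That aim 1 implies 67 markers × 9 fitness tests = 603 tests and about 30 false positives.* That count includes the 14 haematology variables, which the aim does not name.

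It is also fair to say that adjusted logistic models are planned and that the Discussion admits non-random selection and no extrapolation. But the logistic models serve risk profiles and give odds ratios, so they do not answer aims about continuous markers. Limits on extrapolation do not deal with selection bias or chance findings within the sample.

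One could add that 44–49% omission is little more than the lack of power for a small effect. Largely so, but a fixed model would still report the estimate and its interval, without the upward bias.

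**Conclusion.** The point holds as a criticism of a stated method. Forward selection is what the article fixes, and it does not fit aims that name their exposures. Further detail elsewhere could not repair this without replacing the method or forcing the key terms into the model.

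The sizes depend on assumptions that the article does not supply: a true effect of 0.15 SD, ten candidates, entry at 0.05 and the sex differences given above. Larger true effects would be dropped less often and inflated less; more candidates or a looser entry level would admit more noise. The 2.65 chance findings per exposure assume that all 53 nulls are true.

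The unadjusted pairwise tests and the long marker list are a secondary matter. They count because the Discussion and Conclusions read the results as establishing or confirming relationships. The documents do not support saying that confounders are excluded or that confounded findings are bound to be reported. The change is worth making, and it touches only the analysis and the wording.

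**What to change.** Replace forward stepwise regression with one pre-specified model per aim. Each should always retain the named exposure together with sex, age and the pubertal stage already measured. Report the exposure estimate and its interval whatever the P value.

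Present the pairwise and many-marker results as exploratory, or state an error-rate rule such as false-discovery control. Bring the Discussion and Conclusions into line by dropping the language of establishing and confirming for these analyses. Marker families for the error-rate rule, a school term and a second model with adiposity are reasonable choices among several, and the authors can decide on them.

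No new data are needed. The cost is a few degrees of freedom per model and fewer nominally significant results. A strict rule would cost more. For illustration, Bonferroni over all 67 blood markers at n = 200 sets the level at 0.05/67 = 0.00075 and cuts power for a correlation of 0.206 from 83% to 33%. (182 would detect that correlation with an assumed 80% power at two-sided 5%.) That is a reason to prefer false-discovery control or the exploratory label.
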